# Evaluation of the Comparative Efficacy of Aquatherapy Versus Conventional Physiotherapy on Motor Function and Psychosocial Well-Being in Children With Acute Lymphoblastic Leukemia: Protocol for a Randomized Controlled Trial

**DOI:** 10.2196/75877

**Published:** 2025-10-23

**Keywords:** acute lymphoblastic leukemia, aqua therapy, rehabilitation, conventional physiotherapy, motor functions, psychosocial well-being, chemotherapy

## Abstract

**Background:**

Children with acute lymphoblastic leukemia (ALL) undergoing chemotherapy have limited access to rehabilitation support. While rehabilitation on the basis of physiotherapy has been found to enhance psychosocial well-being and motor performance, a viable substitute for this can be aquatherapy. However, no trials have currently evaluated the effectiveness of aquatherapy in this population.

**Objective:**

We aim to evaluate the comparative efficacy of aquatherapy versus conventional physiotherapy on the motor function and psychosocial well-being of children with ALL.

**Methods:**

We will conduct a parallel, single-blinded (participant-blinded), randomized controlled trial with embedded quantitative analysis. In total, 54 survivors of ALL undergoing chemotherapy will be recruited from the Acharya Vinoba Bhave Rural Hospital in Sawangi (Meghe), Wardha, Maharashtra, India. The experimental group will attend a 4-week, thrice-weekly, 45-minute aquatherapy session focusing on exercise-based rehabilitation. The comparison group will receive conventional physiotherapy including standardized exercises. Assessments will be completed at weeks 0 (baseline), 4 (postintervention), and 12 (follow-up). The primary outcome related to motor function will be measured using the timed up and go test and the Pediatric Balance Scale at week 4. Secondary outcomes will include psychosocial well-being measured with the Hospital Anxiety and Depression Scale and functional abilities measured with the Functional Independence Measure for Children (WeeFIM). Health service data, including length of stay in the hospital, hospital readmissions, and emergency department presentations, will be recorded. Semistructured interviews will be completed within an interpretive description framework to explore participant descriptions. The primary outcome will be analyzed using linear mixed effects models.

**Results:**

The trial is scheduled to commence in October 2025.

**Conclusions:**

The trial will inform future implementation of rehabilitation for children with ALL by providing important data regarding the efficacy of aquatherapy compared with conventional physiotherapy as well as patient experience.

**Trial Registration:**

Clinical Trials Registry - India CTRI/2025/03/083036; https://tinyurl.com/v446cd6z

**International Registered Report Identifier (IRRID):**

PRR1-10.2196/75877

## Introduction

Acute lymphoblastic leukemia (ALL) is one of the most common cancers affecting children, with about 64,200 cases reported worldwide. In India, the highest incidence occurs among children aged 2–5 years, with rates of approximately 101.4 cases per million boys and 62.3 cases per million girls [1]. The availability of more advanced therapeutic agents, enhanced supportive care, therapy stratification, and regimen modification in recent times has led to a cure rate of more than 80% and an overall survival probability of 80% to 90%. As a result, awareness about therapy-related morbidity has increased because of the longer survival rates [1].

Acute chemotherapy comprises 2 phases: the induction phase and the consolidation phase. The primary goal of the induction phase is remission. Intense chemotherapy is used during this phase, which typically lasts 4 weeks, to destroy as many leukemia cells as possible. After a successful induction therapy session, patients are moved into the consolidation phase, sometimes referred to as intensification. This phase is aimed at eradicating any leukemia cells that could have remained unaffected during the induction phase. Additional chemotherapy regimens that are different from those used in induction are part of the consolidation phase, which usually lasts many months. This is the most intense phase, requiring a prolonged hospital stay. Children with ALL are considerably less active during the acute stage, usually presenting with deficits in fatigue and activity tolerance [2,3]. They may also exhibit motor deficits as a side effect of the chemotherapy drugs, which include anthracyclines and vincristine. While anthracycline-induced cardiotoxicity reduces aerobic capacity, vincristine-induced neuropathy impairs peripheral sensory and motor function [4,5]. Chemotherapeutic drugs such as vincristine have an adverse effect on balance, which may occur through diverse mechanisms such as by decreasing muscular strength and flexibility or producing cognitive impairment [1]. When used on children with ALL, these drugs can result in self-imposed or medically prescribed activity restrictions, which would lead to routinely engaging in lesser physical activity [1,6].

Children with ALL frequently struggle with motor performances, functional movement, and balance, possibly because of deficits in somatosensory, motor, muscular, and cognitive abilities. Numerous studies on children with ALL have examined the effect of exercise regimens on increasing their ankle range of motion, leg and back muscle strength, and cardiovascular fitness [1,7]. However, studies on the impact of therapies aimed at enhancing balance and functional mobility are limited. Furthermore, not enough research has examined their impact during the induction phase, or the acute stage, of chemotherapy. To avoid additional issues related to the disease, physiotherapy interventions conducted in the early stages of the disease can be crucial [1,8]. Such improvements are essential not only for their physical health but also for their psychological well-being, as enhanced mobility can lead to increased participation in daily activities and social interactions.

Exercise in an aquatic environment is part of aquatherapy, or what is known as aquatic treatment; this form of therapy has in recent times drawn much interest as a possible supplement to traditional physiotherapy. The characteristics of water, like buoyancy and resistance, makes it a workout surface that is both supportive and demanding, potentially improving motor function without placing undue strain on the musculoskeletal system. Aquatherapy has demonstrated beneficial benefits on gross motor function and produced enjoyment of physical activity in pediatric groups [9]. In addition to standard physical treatment, aqua-plyometric (plyo) exercises can help long-term survivors of childhood ALL strengthen their bones, increase their functional ability, and enhance their quality of life [10]. One study examined the impact of aquatherapy on performance in children with brain tumors and found that aquatherapy could help their physical performance [11]. However, aquatherapy’s efficacy, especially in children with ALL, remains underexplored.

The primary aim of this randomized controlled trial is to determine the comparative efficacy of aquatherapy versus conventional physiotherapy on motor function in children with ALL during the induction and consolidation phase of their chemotherapy treatment. The secondary aims include determining the comparative efficacy of aquatherapy versus conventional physiotherapy on the (1) psychosocial well-being and (2) quality of life of children with ALL during the induction and consolidation phase of their chemotherapy treatment.

## Methods

### Study Design

We propose conducting a parallel, single-blinded (participant-blinded), randomized controlled trial with embedded quantitative analysis. The experimental group will attend a 4-week, thrice-weekly, 45-minute aquatherapy session focusing on exercise-based rehabilitation (Figure 1). The comparison group will receive conventional physiotherapy, including standardized exercises. Assessments will be completed at weeks 0 (baseline), 4 (postintervention), and 12 (follow-up). Quantitative trial outcomes will be reported in accordance with the CONSORT (Consolidated Standards of Reporting Trials) statement and SPIRIT (Standard Protocol Items: Recommendations for Intervention Trials) checklist (Multimedia Appendix 1) [12].

On the basis of the acute phase of physiotherapy interventions after chemotherapy treatment in pediatric oncology settings, a 12-week follow-up period is chosen. Clinical trials evaluating early functional and psychosocial responses in children with ALL frequently use shorter follow-up periods. Intensive chemotherapy and related side effects are predicted to cause rapid changes in emotional and physical conditions throughout active treatment phases. Without placing excessive burden on children who are already receiving critical medical care, a 12-week timeline enables the capture of early and clinically meaningful gains.

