### Patient Selection and Consent

Eligible participants will be identified by a physiotherapist. For aquatherapy, the potential participants will be advised about the trial by the clinical staff. If a participant consents, and the parents provide their consent as well (Multimedia Appendix 4), the participant will then be assessed by the physiotherapist. Details of the trial and the aquatherapy session will be provided so that any questions that participants or their parents have can be clarified and written informed consent can be obtained.

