The participants will receive an overview of the exercise regimen and study protocols linked to rehabilitation from the physiotherapist who will be evaluating and administering the aquatherapy intervention. The sessions will be for 45 minutes each, with 3 sessions per week for 4 weeks [10,11]. Activities are aimed at improving motor function and psychosocial well-being. The fidelity of the intervention will be monitored by recording the content of the exercise session and duration of the completed sessions. Participants in both groups will also be asked whether they received any exercise-based intervention outside of the trial at the 4-week assessment and follow-up.

**Table 1 table1:** Intervention and comparison group descriptions based on the TIDieR (Template for Intervention Description and Replication) checklist.

	Experimental group	Comparison group
In brief	Aquatherapy rehabilitation	Conventional physiotherapy
Why	Exercise intervention in the aquatherapy machine is safe, effective, and convenient to use for improving the quality of life of individuals with ALL undergoing chemotherapy.	Individuals with ALL undergoing chemotherapy are routinely offered rehabilitation.
What (materials)	Preparations before the aquatherapy session: Avoid a heavy meal before the session Remain well hydrated before the session Maintain water temperature Wear proper clothing before entering the aquatherapy machine Follow general principles for duration, frequency, and intensity to be maintained Provide participant with weight cuff Aquatic therapy machine equipped with an underwater treadmill and adjustable resistance jets	Rehabilitation is delivered using standard physiotherapy techniques without the use of any specialized equipment Rehabilitation focuses on land-based exercises
What (procedures and heath care provider)	Physiotherapist will provide aquatherapy session protocol in written format	Physiotherapist will provide the exercise guidelines
How	Supervised session in aquatherapy machine Digitally controlled aqua machine allows for real-time monitoring of water speed and session duration, ensuring consistency in exercise intensity.	In person
Where	Aquatherapy machine is placed in the pediatric outpatient department Participants receive aquatherapy in the pediatric outpatient department	Participants receive conventional physiotherapy in the hospital (inpatient department) itself

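### The trial is labelled participant-blinded, but its two arms cannot be hidden from children or parents, and no outcome assessor is stated to be masked.

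*Protocol article*

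**What the plan says.** The protocol article states the blinding twice. The abstract has "We will conduct a parallel, single-blinded (participant-blinded), randomized controlled trial", and Study Design has "We propose conducting a parallel, single-blinded (participant-blinded), randomized controlled trial". Neither place names any blinded party other than the participant.

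Table 1, under Experimental Group: Exercise-Based Aquatherapy, describes what each child will experience. For aquatherapy it is "Supervised session in aquatherapy machine", using an underwater treadmill and resistance jets, and on location it says "Participants receive aquatherapy in the pediatric outpatient department". For the comparison arm, "Rehabilitation focuses on land-based exercises", without specialized equipment, in the inpatient department. The frequencies are 3 and 5 supervised sessions a week.

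On assessors, the same section says that participants get an overview of the regimen "from the physiotherapist who will be evaluating and administering the aquatherapy intervention". Patient Selection and Consent has the physiotherapist assess the child once consent is given. Randomization Procedure places baseline measurement before allocation and gives the allocation list to an independent researcher with no part in assessments. No section says who scores the week-4 outcomes or whether that person knows the arm.

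**The concern.** A single-blind label tells readers that one source of bias has been controlled. Here the only party said to be blinded is the one that cannot be. The label would pass into the CONSORT report that Study Design promises, and readers would credit the trial with a safeguard it does not have.

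The outcomes make this matter. Table 2 gives the Pediatric Balance Scale as 14 items graded 0 to 4, which calls for an observer's judgement on each item. The timed up and go is more objective, but it still depends on when timing starts and stops and on the child's effort. The Hospital Anxiety and Depression Scale is a questionnaire, so knowledge of the arm can colour the answers. The Anticipated Findings section shows that the team expects aquatherapy to help. If the people rating at week 4 know the arm, a favourable result cannot be cleanly separated from expectation.

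**Working it through.** The main check is a reading of the text. The arithmetic at the end only gives a sense of scale.

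**1. Can participants be blinded?** Table 1 and the surrounding text set the arms apart on four features that a family can see:

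| Feature | Aquatherapy | Conventional physiotherapy |
|---|---|---|
| Medium | Water machine with treadmill and jets | Land-based, no specialized equipment |
| Place | Outpatient department | Inpatient department |
| Sessions per week | 3 | 5 |
| Interviews about the program (Consumer Perceptions) | Yes, weeks 0 and 4 | No |

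No sham or concealment of the arms is described. Children aged 4 to 18 and their parents will know which arm they are in. The consent text ("Details of the trial and the aquatherapy session will be provided") adds little. It precedes randomization and does not reveal the allocation; the arms themselves do.

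**2. Is anyone else blinded?** The label names only participants. The independent researcher in Randomization Procedure protects allocation concealment, not outcome rating. Because baseline comes before allocation, week-0 ratings are not exposed to knowledge of the arm. The gap concerns ratings after randomization.

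**3. Who rates?** The words "from the physiotherapist who will be evaluating and administering the aquatherapy intervention" can be read as one person both treating and rating outcomes. They can equally mean assessing the child for the intervention or during it. They refer only to aquatherapy and do not mention week 4.

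**4. Scale, under assumed bias.** The inputs from Sample Size Estimation are 27 per group, SD 1.09, difference 1.12, and z-values 1.96 and 1.64.

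- The plan's own figure reproduces: 2 × (1.96 + 1.64)² / (1.12/1.09)² = 24.55, plus 1.96²/2 = 1.92, gives 26.47, rounded up to 27. The blinding point does not change it.
- The standard error of a difference between two group means is SD × √(2/27) = 1.09 × 0.272 = 0.297.
- A rating tilt of b SD, with no true effect, shifts the test statistic by b/0.272. The rejection rate of a two-sided 5% independent t test then comes from the noncentral t distribution with 52 degrees of freedom:

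| Assumed tilt b (SD) | In units of the SD of 1.09 | Shift b/0.272 | Two-sided rejection rate |
|---|---|---|---|
| 0 | 0 | 0 | 5% |
| 0.2 | 0.22 | 0.73 | 11.1% |
| 0.3 | 0.33 | 1.10 | 19.1% |
| 0.4 | 0.44 | 1.47 | 30.3% |

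The values of b are assumptions; the documents offer none. The rates depend only on b and on 27 per arm, so the SD of 1.09 serves only to express the tilt in units.

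**The case against.** Lack of participant blinding is inherent in comparing a water machine with land-based exercise. To that extent the point corrects a label and is not a design failure. This stands, but the label is still wrong as written.

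A reader might go further and infer that the treating physiotherapist scores the outcomes, so that the trial has no blinding at all. The documents do not support that. The phrase about evaluating takes the intervention as its object and sits in a sentence about explaining the regimen. It does not say who rates week 4, and it is silent on the comparison arm. The assessment mentioned in the consent section comes before randomization. Baseline is measured before allocation, and allocation is described as concealed. A condensed article may also leave the assessor's identity to the full protocol. What survives is narrower: the label as published places every assessor outside the stated blinding.

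A reader might also take it as established that bias runs towards aquatherapy by a known amount. That does not follow either. The comparison arm's rater is unidentified, and the sizes above are illustrations.

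Finally, the experimental section says aquatherapy is given on top of conventional physiotherapy, so the contrast may be more than water against land. This does not rescue the label: a child who enters the water machine still knows it, and so does one who never does.

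**Conclusion.** The concern holds in two parts of different strength. The participant-blinded label is contradicted by the protocol article's own description of the arms; this follows from the text and needs no assumption. It is also established that no other party is named as blinded, so ratings of both primary measures after randomization have no stated protection against expectation bias. That a treating physiotherapist will do those ratings is a possibility raised by loose wording, not a stated fact.

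The size of any bias is unknown. The range of roughly 11% to 30% false positives rests wholly on an assumed tilt of 0.2 to 0.4 SD in one direction, 27 analysed per arm and a two-sided 5% t test. The label should be corrected before the trial starts, because it claims a property that the design does not have.

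**What to change.** - In the abstract and in Study Design, replace the single-blind, participant-blinded description with: open-label for participants, parents and therapists. The article's title carries no blinding claim and needs no change.
- In Experimental Group: Exercise-Based Aquatherapy, replace the ambiguous reference to evaluating. Where existing staff allow, state that week-4 Pediatric Balance Scale and timed up and go ratings in both arms are done by a team physiotherapist who is not treating that child and is not told the arm.
- If staffing does not allow this, declare outcome assessment unblinded and add it to Strengths and Limitations, which does not mention it now.
- Keep both stated primary measures. Dropping the rated scale would be a larger trade-off that this point does not require.

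The cost is a change of wording and, if feasible, a rota arrangement among physiotherapists. The documents give no staff numbers, so feasibility is for the team to judge. The sample size and the interventions do not change. The downside is that the stated blinding becomes less favourable.

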**Figure 1 figure1:**
[figure not shown]
CONSORT diagram for aquatherapy and conventional physiotherapy. GP: general practitioner.

### Randomization Procedure

Eligible participants who have fulfilled baseline measurements will be randomly allocated to the aquatherapy group or conventional physiotherapy control group using a concealed method in accordance with a web-based computer-generated randomization program using permuted blocks of participants. Allocations will be prepared before trial commencement by an independent researcher with no role in participant recruitment, trial administration of intervention delivery, or assessments. The trial coordinator will allocate participants after baseline assessment by contacting the independent researcher via email for random group allocation.

### Setting

The trial will be conducted at the Acharya Vinoba Bhave Rural Hospital in Sawangi (Meghe), Wardha, Maharashtra, India, a hospital that offers treatment for ALL survivors. Participants will be recruited from the same hospital.

### Ethical Considerations

The aquatherapy trial has been approved by the Datta Meghe Institute of Higher Education and Research (Deemed to Be University), formerly known as Datta Meghe Institute of Medical Sciences (Deemed to Be University) (ECR/440/Inst /MH/2013/RR-2019 DHR; EC/NEW/INST/2023/MH/0340; DMIHER(DU)/IEC/2025/634) (Multimedia Appendix 2), and is registered under the ICMR-National Institute of Medical Statistics Clinical Trial Registry - India CTRI/2025/03/083036 (Multimedia Appendix 3).

### Patient Selection and Consent

Eligible participants will be identified by a physiotherapist. For aquatherapy, the potential participants will be advised about the trial by the clinical staff. If a participant consents, and the parents provide their consent as well (Multimedia Appendix 4), the participant will then be assessed by the physiotherapist. Details of the trial and the aquatherapy session will be provided so that any questions that participants or their parents have can be clarified and written informed consent can be obtained.

### Inclusion and Exclusion Criteria

Participants who are aged 4 to 18 years [1], have ALL, and are undergoing acute stages of chemotherapy treatment can be included. The children must be ambulatory, can be of either sex, and must be in the induction or consolidation phase of chemotherapy for ALL.

Children (1) who are medically unfit to participate in the exercise session as determined by a physiotherapist or medical practitioner considering published recommendations [13]; (2) who have discontinued chemotherapy; (3) who have been diagnosed with sepsis; (4) who have preexisting cardiovascular disease, acute or chronic respiratory disease, acute or chronic bone, joint, or muscular disorders, neuromotor deficits or genetic disorders; and (5) with auditory or visual impairments are excluded from the trial.

### Intervention

All participants will receive their usual medical care, which may include adjuvant, neoadjuvant, or palliative treatment; specialist, nursing, and other health outpatient appointments (eg, to see a physiotherapist); and visits to their general practitioner.

As a part of the trial, participants will not receive standardized hospital educational materials; however, they will be guided solely through supervised aquatherapy sessions.

A conventional physiotherapy session involves motor function and psychosocial developmental exercises with very little support in comparison with aquatherapy. As a part of the trial, conventional physiotherapy also includes a session for 45 minutes, 5 times weekly, including strength training thrice a week [7,14,15]. All participants will also have the opportunity to discuss their ongoing rehabilitation needs at the end of the 4-week intervention period. They will be provided written information for referral to appropriate local services for ongoing support if required in line with usual practice at the health service.

